## Abstract

**Introduction:**

*Fewer Falls* is a manualised self-management fall prevention programme co-developed for and with ambulatory and non-ambulatory people with multiple sclerosis (PwMS). Findings from a feasibility study indicate the necessity of a full-scale randomised controlled trial (RCT).

**Methods and analysis:**

A parallel-group RCT with a mixed methods process evaluation as well as a cost-effectiveness evaluation will be conducted. We aim to recruit 240 PwMS, who will be stratified by ambulation level and randomised 1:1 in blocks of eight to intervention or control. The group-based self-management fall prevention intervention involves eight 2-hour online synchronous sessions (approximately eight participants/group) facilitated by a licensed healthcare professional and home assignments to be completed by participants between sessions. The setting is online, and participants can be located anywhere in Sweden. The control and intervention groups will also receive a brochure on fall risk factors and fall prevention in addition to their standard MS care and rehabilitation. Data collection will be performed at baseline and 3, 6 and 12 months after the start of the intervention. Falls will be monitored via a short message service every week during 1 year from the start of the intervention. The primary outcome is fall frequency (falls/person/year). Secondary outcomes include injurious falls, falls control, fear of falling, falls self-efficacy, activity curtailment, perceived effect of MS, self-rated health and cost-effectiveness.

**Ethics and dissemination:**

Ethical approval has been obtained from the Swedish Ethical Review Authority (registration numbers 2022-06667-01 and 2023-07723-02). The RCT will adhere to the Declaration of Helsinki. Written consent to participate will be obtained from all participants. Study-related information about participants will be stored securely at Karolinska Institutet. The results will be presented in peer-reviewed journals, through the patient organisation Neuro Sweden, at conferences, and in social media.

**Trial registration number:**

ClinicalTrials.gov, NCT05789225.

STRENGTHS AND LIMITATIONS OF THIS STUDYThis study protocol describes an online group-based, self-management fall prevention intervention featuring group dialogue and individual action plans for both ambulatory and non-ambulatory people with multiple sclerosis (PwMS).The comprehensive process evaluation will yield understanding of implementation and the mechanisms of impact for the intervention.The health economic evaluation will provide unique knowledge as no study has evaluated the cost-effectiveness of fall prevention programmes in PwMS.The online delivery of the intervention may exclude PwMS with low computer/technical skills and low socioeconomic status.

## Introduction

 Multiple sclerosis (MS) is a chronic inflammatory, demyelinating and neurodegenerative disease that typically is progressive in nature.^1^ Several symptoms of MS are known fall risk factors, including impaired balance, gait and cognition.^2 3^ In people with MS (PwMS), approximately 56% experience a fall within 3 months.^4^ Those PwMS who have experienced a fall in the past year have an 82% probability of falling again within 6 months and a 56% probability of an injurious fall.^5^ Falls among PwMS are associated with fear of falling, low health-related quality of life and injuries.^3 6^ Because PwMS frequently experience injurious falls,^7^ the socioeconomic costs for both PwMS and society are potentially high. Surprisingly, there are no studies on costs related to falls in PwMS. However, existing research describing the cost of falls for other patient populations with neurological problems ^8 9^ have suggested the high healthcare costs associated with falls among PwMS.

Despite the recognition that several MS symptoms influences fall risk,^2 3^ most fall prevention interventions for PwMS only address physical impairments. There is a major gap in existing evidence regarding behavioral and environmental influences on fall risk in PwMS. The importance of comprehensive approaches to fall prevention targeting modifiable risk factors through fall prevention programmes for PwMS has been highlighted.^10^ Another major gap in MS falls research is the scarcity of studies that focus on falls among the 25% of the MS population who can walk only a few steps or not at all, ie, are non-ambulatory.^6^ Fall prevention interventions for non-ambulatory PwMS show promising results but are rare.^11 12^ Although ambulatory and non-ambulatory PwMS share the same fall risk factors,^2 13^ new evidence suggests that some fall risk factors are unique to non-ambulatory PwMS.^13^ Thus, fall prevention programmes for PwMS must target the unique needs and multifactorial fall risks of PwMS, with consideration that members of the target audience may be ambulatory or non-ambulatory and typically will experience fluctuations in functional status and disease over time.

To address the wide variety of fall risk factors for diverse patient populations, research has highlighted the benefits of self-management for PwMS.^10^ Self-management has been defined as ‘the individual’s ability to manage the symptoms, treatment, physical and psychosocial consequences, and lifestyle changes intrinsic in living with chronic conditions’.^14^ Self-management is especially important for PwMS due to the daily fluctuations in functioning and the unpredictable nature of the disease. PwMS have identified support for self-management as one of their top 10 research priorities.^15^ Despite the importance of self-management, few randomised controlled trials (RCTs) have evaluated self-management fall prevention programmes for PwMS,^16^,^18^ and none of those trials included definitions of self-management. A scoping review^19^ identified that few RCTs did not favour either intervention or control groups, which displays the importance of further research.

To address the diverse influences of fall risk factors for both ambulatory and non-ambulatory PwMS, RCTs that evaluate the effectiveness of well-described self-management fall prevention interventions are needed. We have therefore used a co-design methodology and developed the online group-based fall prevention intervention *Fewer Falls* together with PwMS and healthcare professionals^20 21^ following the Medical Research Council recommendations for complex interventions.^22^ A feasibility study has been performed,^23^ indicating feasible results (in manuscript). The online synchronous format was decided based on the suggestion of PwMS that online meetings would make participation in the programme possible even when energy levels are low.^21^ Online programmes and applications are becoming more common,^24 25^ as they can involve geographically spread participants at lower costs.^26^ A thorough description of the *Fewer Falls* programme development process has been published.^21^

### Aim and research questions

This study aims to evaluate the effectiveness of the self-management fall prevention programme *Fewer Falls* on falls in PwMS. The hypothesis is that the fall frequency in the *Fewer Falls* intervention group will be lower than that in the control group.

Research questions (RQs):

RQ 1a: Is there a difference in fall frequency between the intervention group and the control group 6 months (primary endpoint) after the start of the intervention?

RQ 1b: Is there a difference in the fall frequency between the intervention group and the control group 12 months (sustainability) after the start of the intervention?

RQ 2: Are there differences in secondary outcomes between the intervention group and the control group?

RQ 3: How do process evaluation components (context, implementation and mechanisms of impact) inform the interpretation of outcomes?

RQ 4: What is the cost-effectiveness of *Fewer Falls* 12 months after the start of the intervention?

## Methods and analysis

### Design

The study will use a parallel-group RCT design with a mixed methods process evaluation as well as a health economic evaluation. The trial is registered at ClinicalTrials.gov (NCT05789225), and any updates to the protocol will be registered.

This study protocol adheres to the Standard Protocol Items: Recommendations for Interventional Trials (SPIRIT) guidelines for reporting intervention trials.^27^

Figure 1 displays the study enrolment, intervention and assessments. The study flow chart is presented in figure 2.

**Figure 1 F1:**
[figure not shown]
Overview of the study. Schedule of enrolment, allocation, intervention and assessments. RQ = research question

**Figure 2 F2:**
[figure not shown]
CONSORT diagram showing the flow of participants through each stage of the trial.

### Patient and public involvement

The intervention was co-developed in close collaboration with PwMS and healthcare professionals through an iterative process. The intervention development process has been previously described,^21^ PwMS representatives from the patient organisation Neuro Sweden have collaborated as project partners in all stages of the study.

### Participants

The inclusion criteria for participation are self-reported diagnosis of MS; age ≥18 years; ability to walk or independently transfer from bed to chair/wheelchair with or without aids, but without assistance of another person (corresponding to ˂7.5 on the Expanded Disability Status Scale); experienced one or more falls during the last year; ability to understand and communicate in Swedish; and access to and self-rated ability to use technical devices for online meetings and falls data submission, that is, computers or tablets with internet access and mobile phones to receive and send short message service (SMS).

The statistical power calculation for the primary outcome, fall frequency, is based on data from our feasibility pilot RCT study (in manuscript). The pilot study included 45 participants, randomised into an intervention or control group. Falls were monitored weekly via SMS for 18 weeks from the start of the intervention. Data from 27 participants who at baseline reported a fall within the previous 3 months were used. Based on the findings of 2.45 falls for the intervention group (n=11) versus 3.69 in the control group (n=16) over a period of 18 weeks, we determined that a sample size of 84 participants per group is necessary to achieve adequate statistical power (0.8, alpha=0.05).^28^

Because an online publication on interventions for people with chronic conditions reported a high attrition and drop-out rate,^29^ we aim to recruit up to 240 participants, allowing for up to a 35% drop-out rate. The sample size is based on a Poisson distribution, which aligns with the nature of our primary outcome falls/person/year.

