### Analysis

#### Data management and statistical methods

##### RQ 1a, RQ 1b and RQ 2: effectiveness study

Intention-to-treat and per-protocol analyses will be performed. Per-protocol analyses will include participants who fulfil content adherence, defined as completion of at least two action plans.

Descriptive statistics will be used to present data, for example, means, medians, frequencies, SD, quartiles and counts. Drop-out analyses of baseline characteristics will be explored with parametric and non-parametric analyses depending on the data level.

The primary analysis for falls (falls/person/year) will be conducted using generalised linear mixed models (GLMM) with a Poisson link function to account for count data distribution and potential overdispersion. The model will include fixed effects for the intervention group and random effects for participant variations over time. Interactions between variables will be included if deemed necessary. Linear mixed model analyses will be used for normally distributed secondary outcomes. For categorical outcomes, GLMM with logistic or ordinal regression will be used, depending on the nature of the outcome (binary or ordinal). The primary endpoint is 6 months after the start of the intervention. In addition, analyses of sustainability of potential effects will be performed after 12 months. Any missing data will be handled using appropriate methods, such as multiple imputation, to ensure robustness in analyses. Analyses will be performed and reported in accordance with the Consolidated Standards of Reporting Trials (CONSORT) guidelines for RCT.^50^ A data management plan is established and stored at the Research Data Office at Karolinska Institutet.

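### The 84 per group for power 0.8 does not follow from the stated Poisson basis, which gives 32; the variance allowance that would yield 84 is not stated

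*Protocol article*

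**What the plan says.** The Participants section of the protocol article gives the effect as "2.45 falls for the intervention group (n=11) versus 3.69 in the control group (n=16) over a period of 18 weeks". The source is a subset of the pilot: "Data from 27 participants who at baseline reported a fall within the previous 3 months were used". From this it states: "we determined that a sample size of 84 participants per group is necessary to achieve adequate statistical power (0.8, alpha=0.05"). It then says: "The sample size is based on a Poisson distribution, which aligns with the nature of our primary outcome falls/person/year". No variance, dispersion or sidedness is given. The recruitment target is up to 240, with a drop-out allowance of up to 35%.

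Three other statements bear on the point:

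- **Eligibility (Participants).** The trial enrols people who "experienced one or more falls during the last year".
- **Recurrence (Introduction).** People with MS who fell in the past year "have an 82% probability of falling again within 6 months".
- **Primary analysis (Data management and statistical methods).** A generalised linear mixed model is planned "with a Poisson link function to account for count data distribution and potential overdispersion", with random effects for participants. The primary endpoint is at 6 months.

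**The concern.** The article gives a result together with its means, error rates and distribution, so the result can be recomputed. It differs from the recomputed figure by a factor of about 2.6. A reader therefore cannot tell how much between-person variation the trial is powered for.

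That matters because fall counts usually vary more between people than Poisson allows, and the analysis section anticipates this. With a rate ratio near 0.66 and control means of several falls, the dispersion term can contribute more to the required sample size than the Poisson term. The Discussion describes the trial as full-scale and powered, so a null result will be read against the stated 0.8. If the dispersion behind 84 is unknown, so is the basis for that reading.

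**Working it through.** **Inputs.** Means m1 = 2.45 and m0 = 3.69 per 18 weeks, power 0.8, alpha 0.05, 1:1 allocation, Poisson (Participants; Recruitment and procedures). Two-sided testing is an assumption. Rate ratio = 2.45/3.69 = 0.664.

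**Step 1: the plan's own figure.** For two Poisson rates on the log scale,

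n per group = (1.960 + 0.842)² × (1/m1 + 1/m0) / [ln(m0/m1)]²

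= 7.849 × 0.6792 / 0.1677 = 31.8, so 32.

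Power at 84 = Φ(0.4095/√(0.6792/84) − 1.960) = Φ(4.555 − 1.960) = 0.995.

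Other forms at power 0.8 on the 18-week means do not recover 84:

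- Rate-difference, square-root and null-variance forms give 31 to 32 two-sided and 24 to 25 one-sided.
- A comparison of two means with a Poisson standard deviation gives 26 to 38, depending on which mean supplies it.
- Two-sided power of 0.9 gives 42 to 43 per group. There 84 would be roughly the total, contrary to both the per-group wording and the 0.8.

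**Step 2: what 84 would need.**

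- Overdispersion factor: 84/31.8 = 2.64.
- Negative binomial, variance μ + kμ²: n = 7.849 × (1/m1 + 1/m0 + 2k)/0.1677. Setting n = 84 gives 0.6792 + 2k = 1.795, so k = 0.56.

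**Step 3: is Poisson compatible with the Introduction?** The pilot control rate carried to 26 weeks is 3.69 × 26/18 = 5.33. Under Poisson, the share with at least one fall is 1 − exp(−5.33) = 99.5%. The cited share within 6 months is 82%. At a mean of 5.33, a negative binomial leaves 18% without a fall when (1 + 5.33k)^(−1/k) = 0.18, which gives k = 1.14.

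**Step 4: power if the 82% is held.** The 82% describes people with a fall in the past year. The 5.33 comes from a subset with a fall in the previous 3 months, so the trial's control mean may be lower. I hold 82% and the rate ratio of 0.664, vary the 26-week control mean M (an assumption), solve k each time, and compute

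power = Φ(0.4095/√[(1/(0.664M) + 1/M + 2k)/n] − 1.960).

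| M (26 weeks) | k | n per group for 0.8 | Power, 78 per group | Power, 84 per group | Power, 120 per group |
|---|---|---|---|---|---|
| 1.72 | 0.004 | 69 | 0.85 | 0.87 | 0.96 |
| 2.5 | 0.42 | 86 | 0.76 | 0.79 | 0.91 |
| 4 | 0.88 | 112 | 0.65 | 0.68 | 0.83 |
| 5.33 | 1.14 | 129 | 0.59 | 0.62 | 0.77 |

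The 120 column is all 240 analysed. The 78 column is 240 × 0.65 = 156, that is 78 per group after the full drop-out allowance. A simulation with 84 per group at M = 5.33 and k = 1.14, analysed by negative binomial regression, gave power 0.62, in line with the formula.

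**The case against.** The strongest defence is that the mismatch is conservative. The figure used is 2.6 times the Poisson requirement, so the trial was not sized as though overdispersion were absent. A variance allowance may have been applied and lost when the article was condensed. The cited method reference and the pilot manuscript, which might show it, are not available here. A Poisson mixed model with participant random effects does accommodate overdispersed counts, so the analysis section does not contradict the sample size section. All of this stands. It makes an undisclosed allowance likely, but it leaves the text as written unable to produce its own number.

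A reader might go further and infer that the 82% shows the true power to be about 0.6. The document does not support that:

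- The calculation joins a cited cohort defined by a fall in the past year to a pilot mean from 16 controls defined by a fall in the previous 3 months. A lower mean in the trial population could explain part or all of the gap between 82% and 99.5%.
- It assumes a constant rate and a negative binomial form, and it is sensitive to the non-faller share. At mean 5.33 with 10% non-fallers instead of 18%, k is 0.65 and power at 84 per group is 0.81.
- It takes 84 per group as analysed. The target is 240, and participants who discontinue are asked to keep answering the SMS.

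A reader might also fault the 18-week horizon against a 6-month endpoint. It does no harm: at k = 1.14, power at 84 per group is 0.59 on the 18-week means and 0.62 on the 26-week means.

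**Conclusion.** The point holds as a failure of the stated figure to follow from its stated basis. The Poisson inputs give 32 per group at two-sided 0.05 and power 0.8, and 84 would give about 0.995. None of the forms tried gives 84 per group at power 0.8 on the 18-week means. Reaching it takes an unstated variance factor of about 2.6 (negative binomial k about 0.56). Either the Poisson description or the number needs correcting.

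Loss of power is a conditional risk and is not established. If 82% of controls fall within 6 months and the rate ratio is 0.664, power at 84 per group is about 0.87 at a 26-week control mean of 1.72, 0.79 at 2.5, 0.68 at 4 and 0.62 at 5.33. At 5.33 it is 0.77 if all 240 are analysed. These figures assume a negative binomial form with common dispersion in both arms. The documents do not fix where in this range the trial lies; the pilot's participant-level counts would help to narrow it.

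**What to change.** In the Participants section, replace the Poisson statement with a negative binomial or explicitly overdispersed calculation for the 6-month window. State:

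- the formula and whether the test is one- or two-sided;
- the control rate and rate ratio, and how a rate from the subset with a fall in the previous 3 months carries over to a population with a fall in the past year;
- the dispersion estimated from the pilot's participant-level SMS counts, or, if 84 already contains an inflation factor, that factor.

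In place of the unqualified 0.8, report the power that 240 recruits deliver over a plausible range of dispersion, both with all analysed and after the allowed drop-out.

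The cost is a recalculation from pilot data that the sponsor should already hold, and an update of the wording in the protocol and registry. No extra participants and no change to trial conduct are needed. The stated power may become less favourable.

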### Recruitment and procedures

Participants will be recruited via flyers placed in inpatient and outpatient MS and rehabilitation clinics, from social media advertisements published by Karolinska Institutet, and by the patient organisation Neuro Sweden.

The notices will include a link to a webpage with study information and an online template where interested individuals can fill in their contact information. A research assistant with training in Good Clinical Practice^30^ will screen the completed templates regularly, contact potential participants by phone or e-mail (depending on PwMS’ choice of contact), and provide potential participants with information about the study. Individuals expressing interest in the study will be screened for eligibility. The informed consent process will be initiated with PwMS who meet the eligibility criteria. Specifically, eligible PwMS will be sent written information. Informed consent (online supplemental material) is obtained through BASS, an integrated online treatment and assessment platform. The platform is provided by the eHealth Core Facility at Karolinska Institutet, Stockholm, Sweden. Individuals providing informed consent will be included.

Baseline assessment will be supported by the use of the BASS database. The PwMS will subsequently be randomised to the intervention group or the control group using a data-generated system (Sealed Envelope Ltd. 2021). Participants will be stratified as non-ambulatory (able to walk a maximum of 5 m with assistance or not able at all) or ambulatory in a 1:1 allocation ratio of blocks of eight. Participants will be contacted by phone to inform them about group allocation.

Recruitment began in December 2023, and the expected completion of the study is January 2027. An overview of the study schedule of enrolment, allocation, intervention and assessments are presented in figure 1.

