The primary outcome of *Fewer Falls* is fall frequency.^40^ The primary endpoint is 6 months after the start of the intervention. However, falls will be monitored in both intervention and control groups from the start of the *Fewer Falls* programme until 12 months after the start of intervention, as recommended in fall prevention literature.^41^ An online SMS will be sent to the intervention and control participants once a week asking, ‘Have you fallen within the last week?’ The total number of falls, number of fallers and injurious fall incidence^40^ will be recorded. Participants answering ‘yes’ to the weekly SMS will receive a questionnaire through BASS that includes a series of questions about fall-related injuries. A fall is defined as ‘an unexpected event in which the participants come to rest on the ground, floor or lower level’.^41^ Secondary outcomes, collected at baseline and 3, 6 and 12 months after the start of intervention, are sense of control of falls prevention assessed by the Falls Control Scale^42^ (administered to all participants), a direct measure of fear of falling^43^ and falls self-efficacy assessed by the Short Falls Efficacy Scale-International^44^ (administered to ambulatory participants), the Spinal Cord Injury Falls Concern Scale^45^ (administered to non-ambulatory participants) and a revised version of the Short Falls Efficacy Scale-International^46^ (administered to all participants). The following are also administered to all participants to collect data: activity curtailment assessed by a single question,^43^ perceived impact of MS assessed by the Multiple Sclerosis Impact Scale^47^ and self-rated health assessed by the EuroQol-5D-5L.^48^

Participants who discontinue the intervention will be contacted and asked if they are willing to continue responding to the SMS and questionnaires.

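### The 35% drop-out allowance does not fit the stated sample size: 240 recruits cover at most 30% loss from a requirement of 84 per group

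*Protocol article*

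**What the plan says.** The Participants section of the protocol article derives the sample size from the pilot trial: "2.45 falls for the intervention group (n=11) versus 3.69 in the control group (n=16) over a period of 18 weeks". From this it concludes that "a sample size of 84 participants per group is necessary to achieve adequate statistical power (0.8, alpha=0.05"). The next paragraph cites reported high attrition in online interventions for people with chronic conditions and continues: "we aim to recruit up to 240 participants, allowing for up to a 35% drop-out rate". It adds: "The sample size is based on a Poisson distribution". Under Recruitment and procedures, participants are randomised within ambulation strata "in a 1:1 allocation ratio of blocks of eight", so 240 recruits means 120 per group. The article gives no lower required number and no other rule for allowing for drop-out.

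**The concern.** Three figures stand in two consecutive paragraphs: 84 per group required, 240 recruited, and 35% loss allowed for. Any two of them fix the third, and the three printed values do not agree. The allowance is there because the authors expect that attrition may be high, so loss between 30% and 35% is a range they treat as plausible. In that range the number remaining falls below the number the protocol calls necessary, while the text says the range is covered. Anyone who later judges observed attrition against 35% would be using the wrong threshold.

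**Working it through.** **Inputs.** Required number: 84 per group at power 0.80 and alpha 0.05 (Participants). Recruitment target 240 and drop-out 35% (Participants). Allocation 1:1 (Recruitment and procedures). Pilot means 2.45 and 3.69 falls over 18 weeks (Participants). The article does not say whether the test is one- or two-sided; two-sided is assumed unless noted.

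**Step 1: does 240 follow from 84 per group and 35%?**
- Required in total: 2 × 84 = 168.
- Recruits needed at drop-out d: 168/(1 − d). At d = 0.35 this is 168/0.65 = 258.5, so 259, or 260 with equal groups (84/0.65 = 129.2, so 130 per group).
- The stated 240 is not reproduced.

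**Step 2: what does 240 leave at 35%?**
- 240 × 0.65 = 156, or 78 per group.
- Shortfall: 168 − 156 = 12 in total, 6 per group.

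**Step 3: what drop-out does 240 cover?**
- 1 − 168/240 = 1 − 0.70 = 0.30, exactly 30%.

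**Step 4: where might 240 come from?** Multiplying by 1 + d instead of dividing by 1 − d gives 84 × 1.35 = 113.4 per group. Rounded up to whole groups of eight, this is 15 × 8 = 120 per group, or 240 in total. That fits the group size of about eight and the roughly 15 programme cycles in the Intervention section. The article does not state its rounding, so this is only a possible explanation. It would not make a 35% loss safe, because 78 per group still remain.

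**Step 5: conditional effect on power.** Take 84 per group as exactly 80% power and hold everything else fixed:
- Power at 78 = Φ(√(78/84) × (1.960 + 0.842) − 1.960) = 0.770, about 77%.
- The one-sided version gives 0.774.

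**Step 6: is 84 itself firm enough to carry that figure?** Under a plain two-sample Poisson model, n per group = (1.960 + 0.842)² × (2.45 + 3.69)/(3.69 − 2.45)² = 31.3. The log-rate version gives 31.8. So about 32 per group would suffice for 80% (42 to 43 for 90%), and 78 per group would have about 99% power. Reaching 84 needs a variance about 2.6 to 2.7 times the Poisson variance, and the article states no such factor.

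**The case against.** A reader might infer from the shortfall that the trial misses its 80% power, or that 77% is the protocol's own figure at 35% attrition. The documents support neither, for three reasons.

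- The 77% rescales from 84, and 84 does not reproduce from the stated means on the stated Poisson basis.
- The 84 rests on 18 weeks of counts, whereas "The primary endpoint is 6 months after the start of the intervention", about 26 weeks. If information grew with person-time, 78 × 26 = 2,028 person-weeks per group would exceed 84 × 18 = 1,512 by about 34%. Overdispersion would shrink that gain. The pilot subset had fallen within the previous 3 months while the trial admits people with a fall in the past year, which may work the other way. The net direction is unknown.
- Drop-outs need not contribute nothing. Falls are reported weekly by SMS, participants who stop the intervention are asked to keep responding, and the Analysis section plans intention-to-treat analysis and names multiple imputation as a way of handling missing data. So 78 analysed per group is a worst case.

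All of this stands against a firm power claim. None of it repairs the sentence: the Participants section does not use longer exposure, partial data or imputation to lower the required 84. Reading both figures as upper limits does not help either. An allowance of up to 35% includes 35%, and recruiting fewer than 240 would leave less room for loss.

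**Conclusion.** Wrong as written; a minor correction to a stated design figure. Given the protocol's own requirement of 84 per group and 1:1 allocation, 240 recruits cover at most 30% drop-out, and at 35% the number remaining is 12 short in total. This conclusion needs only the printed figures, with drop-out read as the share of recruits lost. The fall from 80% to about 77% holds only if 84 is exactly the 80% point and nothing else changes, so it illustrates the scale and is not a finding about the trial's actual power. The unstated variance assumption behind 84 is a separate matter. The comparison of groups, the analysis and the recruitment target are unaffected.

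**What to change.** In the Participants section, keep the target of 240 and replace 35% by 30% in the drop-out sentence. If the sponsor prefers to keep 35%, add that this leaves 78 per group, below the stated requirement of 84. A power of 77% should not be printed alongside unless the variance assumption that yields 84 is stated too. Either change is one sentence, makes a stated figure slightly less favourable and needs no extra participants. Holding both 84 per group and 35% would instead take 260 recruits, 20 more than planned; the correction does not require this.
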